### Study variables

2.5

The study variables are as follows:

Age at inclusion.Sex.Duration of symptoms (in months).Etiology of BPPV.Affected ear.Nystagmus latency during the Dix-Hallpike Test (DHT) (in seconds).Nystagmus duration during the DHT (in seconds).Mean slow-phase velocity of the vertical component of nystagmus during the DHT (in degrees/s).Dizziness Handicap Inventory (DHI) score at inclusion and 6 months after inclusion.Resolution of symptoms after treatment (yes or no).Resolution of nystagmus (PRIMARY VARIABLE) after treatment (yes or no).Number of consultations required for resolution (to quantify the reduction in healthcare resources).

### Data collection

2.6

Even if intermediate visits are necessary, the following study visits will be conducted according to the protocol (with data recording):

Visit 1 (eight weeks after inclusion):

The Dix-Hallpike Test (DHT) will be performed with videonystagmographic recording. If positive:In the control group, the conventional Epley maneuver will be repeated using a mechanized chair.In the study group, a personalized Epley maneuver will be performed using a mechanized chair.

Visit 2 (ten weeks after inclusion):

The DHT will be repeated with videonystagmographic recording. If positive:In the control group, the conventional Epley maneuver will be repeated using a mechanized chair.In the study group, the personalized Epley maneuver will be repeated using a mechanized chair.These maneuvers (conventional for the control group and personalized for the study group) will be repeated every two weeks until resolution of symptoms (or up to a maximum of 8 repetitions).

Visit 3 (Six months after inclusion):

The following variables will be recorded:Dix-Hallpike Test (DHT) results (negative or positive).Dizziness Handicap Inventory (DHI) score.Number of consultations required for resolution.

### Mathematical study

2.7

A 3D model of the affected membranous labyrinth will be reconstructed based on MRI imaging. An analysis of the planes on which the semicircular canals rest will be performed, and the geometric model will be adapted for subsequent numerical simulation.

The primary requirement of the MRI is that the scan must be a volumetric sequence (with very thin slices and no gaps between them), fluid-sensitive (T2-weighted), and must include the eyeballs within the field of view to provide a reference for identifying the Frankfurt plane.

The computational study, carried out using Computational Fluid Dynamics (CFD) techniques, will involve combining the dynamics of the endolymph within the labyrinth and the particle dynamics of the free otoliths.

Mathematically, the Navier–Stokes equations will be coupled with a discrete particle model sensitive to gravity and the fluid forces. This will allow for the determination of the velocity distribution of the endolymph, the pressures exerted on the labyrinth walls, as well as the timing and positions of the otoliths during the personalized Epley maneuver.

Notably, the simulations were performed using Star CCM+, a widely recognized computational fluid dynamics (CFD) solver used in both research and industry. While other tools exist for real-time “simulation,” in our opinion, they lack the precision required for detailed biomechanics and particle-fluid interactions, which are critical for accurately modeling otoconial displacement.

The primary objective of the fluid simulation is to optimize the maneuver angles for treating BPPV. While canal alignment is an important factor, the simulation extends beyond anatomical variations by also considering fluid dynamics and otolith behavior during repositioning maneuvers.

In other words, successful BPPV treatment is not solely determined by canal orientation but rather by the complex interplay of forces acting on the fluid and otoconia. The CFD model allows us to predict how otoconia move within the semicircular canals under different maneuver conditions, enabling us to tailor the maneuver angles accordingly.

We expect that this more accurate approach, combined with the precise anatomical data of each refractory patient, will enhance treatment outcomes.

The final version of our mathematical model represents a balance between computational cost and accuracy, ensuring precise simulation of fluid and otoconia dynamics. For instance, large displacements—such as those involving full-body rotations from the waist—introduce inertial forces that can alter the trajectory of otoconia. This effect can lead to different final otoconia positions after 30 s of resting time, which in turn impacts the effectiveness of repositioning maneuvers.

Our analysis considers variations of 9° in the excursion angle of both rotational arms of the mechanical chair. We consider that the error margin inherent in these models is contained within this range, as previous simulations showed that variations in different parameters resulted in deviations smaller than this threshold.

To identify the optimal maneuver, we simulate different otoconial sizes and select the configuration that facilitates the greatest otoconial displacement toward the exit of the posterior canal. In the final steps—once the otoconia exit the canal—we ensure their translation toward the utricular macula for complete repositioning.

By incorporating these factors, our CFD-based approach enables a more precise and individualized treatment strategy for refractory BPPV cases.

We ensured reproducibility by conducting repeated simulations using the same patient’s vestibular anatomy. We ran hundreds of simulations, testing different solvers, meshes, boundary conditions, and other parameters related to vestibular physiology. Based on this analysis, we concluded that our model has certain limitations, such as assumptions regarding particle shape, particle interactions, and wall conditions, among others. These limitations and more information about this mathematical model, designed for studying BPPV treatment, are discussed in detail in our previous study (22).

### Data analysis

2.8

Demographic data and patient characteristics will be described globally and by relevant covariables.

Continuous outcomes will be summarized using mean, median, standard deviation (SD), and interquartile range (P25, P75). For categorical outcomes, the number and percentage of patients in each category will be reported. Statistical analyses will be based on the full analysis set (FAS), which includes all randomized participants who provided informed consent and met all inclusion criteria without any exclusion criteria. The analysis will follow the intention-to-treat principle.

The key outcome variables of interest are:

Resolution of nystagmus (yes vs. no), which is the primary outcome.Resolution of symptoms (yes vs. no).DHI score (minimum: 0; maximum: 100) at inclusion and 6 months after inclusion.Number of consultations required until resolution.

Covariables of interest include:

Baseline patient characteristics:Sex.Age at inclusion.Nystagmus latency period during the Dix-Hallpike Test (in seconds).Nystagmus duration during the Dix-Hallpike Test (in seconds).Mean slow-phase velocity of the vertical component of nystagmus during the Dix-Hallpike Test (in degrees/s).Associated risk factors:Duration of symptoms.Etiology.Adherence to the intervention (direct observation by the investigator in both intervention arms).

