### Study design

2.1

This is an experimental, multicenter, open-label, randomized study (using balanced block randomization) with two parallel arms. The study targets patients with a definitive diagnosis of refractory posterior semicircular canal BPPV (BPPVp).

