### Study participants

2.2

*Study period*: From January 1, 2024, to December 31, 2026.

*Study population*: Patients diagnosed with BPPV.

*Target population*: Individuals >18 years of age, of both sexes, diagnosed with unilateral refractory BPPVp, from three Health Areas. Participants will be selected from patients attending the Otoneurology Unit of the Otolaryngology Departments of these three University Hospital Complexes.

*Inclusion criteria*: Participants must understand the study objectives, agree to participate, and sign the informed consent form. Candidates must meet the following two requirements:Diagnosed with BPPVp according to the Barany Society criteria:Recurrent episodes of vertigo or positional instability, triggered by lying down or turning the head in the supine position.Episodes lasting less than 1 min.Positional nystagmus observed after a latency period during the Dix-Hallpike test (DHT), with an upward vertical component and a torsional component (clockwise on the left side and counterclockwise on the right).Symptoms not explained by any other cause.Refractory to otolith repositioning maneuvers (Epley and/or Semont maneuvers), with persistence of symptoms after three attempts.

*Exclusion criteria*: Participants will be excluded if they have:Cognitive impairment that prevents understanding of their condition and the required procedures.Pathological conditions that hinder the execution of the maneuvers.BPPV involving canals other than the posterior canal or bilateral posterior canal involvement.Patients who fail to demonstrate two successful repetitions of Brandt-Daroff maneuvers when provided with one set of verbal instructions and once set of printed instructions.

To confirm the diagnosis and rule out other potential causes, all participants will undergo a complete otoneurological evaluation, including:

Otoscopy.Basic neurological examination.Observation of spontaneous nystagmus (with and without gaze fixation).Clinical head impulse test (vHIT), including video-assisted evaluation.Positional tests (DHT, McClure test, and head hyperextension), with videonystagmographic recording.Pure-tone audiometry.

In cases of refractory BPPV (lack of resolution after three therapeutic maneuvers), a magnetic resonance imaging (MRI) scan of the inner ears and posterior cranial fossa will be requested to rule out central neurological causes.

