### Randomization process

2.4

*Visit 0 (Randomization visit)*: After obtaining consent, participants will be randomized to one of the following study arms:

Control group: Participants will be advised to perform Brandt-Daroff exercises at home twice daily for 8 weeks. An MRI of the inner ear and posterior cranial fossa will also be requested. If the exercises are ineffective, repositioning maneuvers will be repeated biweekly until symptom resolution using a mechanical rotational chair, specifically the Thomas Richard Vitton (TRV) reposition chair.Study group: Participants will perform Brandt-Daroff exercises at home twice daily for 8 weeks. An MRI will be conducted, and based on the images, a personalized mathematical model will be created to modify the angles of the repositioning maneuver. If the exercises are ineffective, the personalized maneuver will be performed using a mechanized chair.

A balanced block randomization sequence with block size n = 10 will be generated by a member of the research team.

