### Study limitations, data biases, and mitigation strategies

2.9

Despite being an open-label study, the potential bias introduced is minimal, as both the maneuvers and outcome evaluation are performed by the same person. The primary outcome (resolution of nystagmus) is assessed objectively through videonystagmography, which does not require interpretation by the evaluator.

There is a risk of patient dropout during the eight-week period of Brandt-Daroff exercises prior to the personalized maneuver. To mitigate this risk, patient adherence will be closely monitored and encouraged with reminders and follow-ups.

Since patients will be recruited from three different hospitals, there may be diagnostic biases depending on the evaluator. However, all intervention maneuvers (both personalized and conventional) will be conducted at a single center, where a diagnostic reevaluation will be performed prior to intervention to confirm that the BPPV remains unresolved and exclusively affects the posterior canal.

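### The full analysis set removes randomized participants who fail an eligibility criterion, which conflicts with the stated intention-to-treat principle and leaves room for exclusions based on findings made after open allocation

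*Protocol article*

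**What the plan says.** Section 2.8 (Data analysis) bases the statistical analyses on the full analysis set: "FAS), which includes all randomized participants who provided informed consent and met all inclusion criteria without any exclusion criteria". The next sentence reads: "The analysis will follow the intention-to-treat principle".

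Four other parts of the article determine when eligibility is known and who knows the arm:

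- **Masking and timing of allocation.** Section 2.1: "This is an experimental, multicenter, open-label, randomized study (using balanced block randomization) with two parallel arms". Section 2.4, for Visit 0: "After obtaining consent, participants will be randomized to one of the following study arms".
- **MRI.** Section 2.4 lists it under the allocated arms. For the control group: "An MRI of the inner ear and posterior cranial fossa will also be requested". For the study group it is conducted and its images feed the personalized model. Section 2.2 gives the scan a diagnostic purpose: "a magnetic resonance imaging (MRI) scan of the inner ears and posterior cranial fossa will be requested to rule out central neurological causes". The inclusion criteria in that section require that no other cause explains the symptoms.
- **Diagnostic re-evaluation.** Section 2.9 says that, at the single treating center, "a diagnostic reevaluation will be performed prior to intervention to confirm that the BPPV remains unresolved and exclusively affects the posterior canal". Section 2.6 places the first maneuver at Visit 1, eight weeks after inclusion. Section 2.2 lists involvement of another canal, or of both posterior canals, as an exclusion criterion.
- **Assessor.** Section 2.9 says that one person performs both the maneuvers and the outcome evaluation.

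**The concern.** Randomization protects the comparison only for the groups that were randomized. Removing patients for ineligibility can be harmless if the failure was already a fact at randomization and is judged by someone who does not know the arm. Section 2.8 sets neither condition.

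In this trial the gap has practical content. A scan read after allocation could be taken to overturn the criterion that no other cause explains the symptoms. A week-8 examination could be taken to show an excluded canal pattern. Both would be judged in an open-label setting, with no masked eligibility decision described. Scrutiny could also differ by arm, because only study-group images are described as being turned into a model.

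At stake is who counts in the primary comparison, with 27 patients per arm. Videonystagmography makes the measurement of nystagmus objective, but it does not govern the decision on who is counted.

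**Working it through.** **1. The two statements in section 2.8.** The set requires four things: randomized, consented, every inclusion criterion met, no exclusion criterion present. Intention-to-treat, taken as stated, requires only the first and analysis as allocated. They agree only if no randomized patient is ever found ineligible.

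**2. Can a patient be found ineligible after randomization?**

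| Information | Section that times it | Criterion it could touch (section 2.2) | After allocation? |
|---|---|---|---|
| MRI for central causes | 2.4, under the arms; 2.2, next to the diagnostic work-up | Symptoms not otherwise explained | Yes by 2.4; unclear by 2.2 |
| Re-evaluation: posterior canal only | 2.9, before the maneuver; first maneuver at week 8 by 2.6 | Other canal or bilateral disease | Yes |
| Re-evaluation: still unresolved | as above | None listed | Not applicable |

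The second row is enough on its own. Even if the MRI came before allocation, the canal check would not.

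**3. The plan's own sample size.** Inputs from section 2.10: 25% versus 75%, two-sided α = 0.05, power 95%. With pooled variance and no continuity correction:

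n = [1.960·√(2·0.5·0.5) + 1.645·√(0.25·0.75 + 0.75·0.25)]² / 0.50² = (1.386 + 1.007)² / 0.25 = 22.9, so 23 per arm, as stated. The stated 27 per arm follows from 23 × 1.15 = 26.45, rounded up. That margin is described as covering dropout; eligibility exclusions are not mentioned. Power at 27 per arm is 97.6%.

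**4. Cost of keeping everyone.** Suppose m of the 27 study-group patients are true ineligibles who resolve at the control rate of 25% (m is assumed; the article gives no figure). The expected difference is 50 × (27 − m)/27 points:

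- m = 1: 48.1 points, power 96.4%
- m = 2: 46.3 points, power 94.8%
- m = 3: 44.4 points, power 92.8%

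**5. How sensitive 27 per arm is to a few exclusions.** This is a worst-case illustration, not an estimate. Assume no true difference, a common resolution rate of 25% or 50%, a pooled two-sided z-test at 5%, and exact binomial enumeration. The chance of a significant result favoring the study group is 2.8% (rate 25%) or 2.1% (rate 50%) with no exclusions. If two non-resolved study-group patients are dropped, it is 4.1% or 5.3%. Both the number dropped and the dependence on outcome are assumed.

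**The case against.** The strongest reply is that having met the criteria naturally means having met them at entry. Section 2.3 fixes much of this before randomization: canal status is tested at the pre-selection visit, and the three failed maneuvers are verified in the medical record. On that reading a canal change at week 8 is a new event, and the check in section 2.9 only guards the maneuver and evens out diagnostic differences between hospitals. Nothing says that a patient failing it leaves the analysis. This is a fair reading, and it limits the point to what the wording permits. It does not remove the point, because section 2.8 does not say that eligibility is judged on entry data.

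MRI timing is also open. Section 2.2 can be read as placing the scan in the work-up before inclusion. The two sections must be reconciled, but the canal check follows allocation on either reading.

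Three stronger inferences are tempting and are not supported:

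- **That patients who resolve on the exercises can leave the set.** No listed criterion excludes them. Sections 2.4 and 2.6 provide for early resolution by making the maneuver conditional on continuing disease.
- **That a few decisions at the re-evaluation would raise an observed rate sharply**, for example from 20/27 (74.1%) to 20/24 (83.3%). The check precedes the first maneuver, and until then both groups are assigned the same exercises, so final non-resolvers cannot be picked out at that point. Any such count is invented. The same caution applies to the illustration in step 5 of the working.
- **That the primary comparison will be adjusted for adherence.** Section 2.8 lists "Adherence to the intervention (direct observation by the investigator in both intervention arms" among covariables of interest but states no adjusted model.

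Finally, excluded patients could still be counted by arm and put back in a sensitivity analysis, so a bias would not necessarily stay hidden.

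**Conclusion.** The point holds as a conflict in the text with a real route behind it. Section 2.8 restricts the primary set by eligibility and claims intention-to-treat, and other sections show eligibility-relevant findings arising after open allocation. The wording permits arm-aware exclusions; the article does not say that they will happen.

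Neither the direction nor the size of any bias can be computed, because the article gives no expected number of ineligible patients and no rule for removing them. What can be shown is that the correction is cheap: the planned 54 patients are unchanged, and with one to three true ineligibles retained in the study group, power stays between 96.4% and 92.8% under the assumptions in the working. The conclusion rests on the wording of section 2.8 and on the post-allocation timing of the canal check; it does not depend on how the MRI timing is resolved.

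**What to change.** In section 2.8, define the primary analysis set as all randomized participants, analysed in the arm to which they were allocated. State that a change of canal found at Visit 1, or an MRI finding after allocation, does not remove a patient from it.

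If any exclusion is kept, limit it to an eligibility failure documented entirely from data recorded before randomization and judged without knowledge of arm or outcome. Report the eligibility-restricted set as a sensitivity analysis only, with the number and reason for each exclusion by arm.

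Reconcile sections 2.2 and 2.4 on when the MRI takes place relative to allocation.

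The cost is one paragraph in section 2.8 and a clarification of the MRI sequence. A few true ineligibles may stay in and dilute the effect slightly; the sample size does not change.

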The secondary objectives are:

To determine whether there are differences at the time of diagnosis (mainly in the characteristics of nystagmus) between patients with refractory BPPV and those who respond well to conventional maneuvers.To develop software capable of generating a mathematical model based on MRI images of the patient’s inner ear, predicting the movement angles necessary to guide the otoliths back to the vestibule. This model will also provide additional information that can be used to rule out or confirm the presence of other underlying pathologies.To quantify the potential reduction in the subjective perception of disability achieved by performing modified, personalized maneuvers compared to the repetition of conventional maneuvers and Brandt-Daroff exercises.To quantify the reduction in healthcare resources (primarily in the number of consultations) achieved through treatment with personalized maneuvers.

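### The consultation outcome has no value for patients who never resolve, so as defined it cannot be analysed by intention to treat or measure healthcare use

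*Protocol article*

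**What the plan says.** The last secondary objective in the Introduction is "To quantify the reduction in healthcare resources (primarily in the number of consultations) achieved through treatment with personalized maneuvers". The variable serving it is listed in section 2.5 as "Number of consultations required for resolution (to quantify the reduction in healthcare resources". Section 2.6 records the same item at "Visit 3 (Six months after inclusion", and section 2.8 lists it among the key outcomes as "Number of consultations required until resolution".

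Section 2.6 also shows that unresolved patients are foreseen. Maneuvers start at "Visit 1 (eight weeks after inclusion" if the Dix-Hallpike test is positive, and continue every two weeks "until resolution of symptoms (or up to a maximum of 8 repetitions". Section 2.10 assumes that about 25% of controls are cured, by repeated maneuvers or by Brandt-Daroff exercises, against 75% in the study arm.

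On the population, section 2.8 says: "Statistical analyses will be based on the full analysis set (FAS), which includes all randomized participants" (with consent and eligibility conditions), and "The analysis will follow the intention-to-treat principle". No section says what value the consultation variable takes in a patient who has not resolved.

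**The concern.** A count that runs up to an event exists only where the event occurs. Here the event is the treatment's intended effect, and the design assumes that it differs between arms by 50 percentage points. The patients without a value are mostly controls, and they are likely to be the heaviest users of consultations.

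Two things are at stake.

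- **Population.** An intention-to-treat analysis needs a value, or an explicit rule such as censoring, for every patient in the set. If the definition is simply followed, the resolvers in each arm are compared. They are selected by a post-randomization outcome, so the comparison loses the protection of randomization.
- **What is measured.** The objective concerns healthcare resources. A count that stops at resolution omits all consultations of patients who stay unresolved, and any later consultations of patients who resolve and then relapse. The Discussion cites recurrence rates of 11 to 27.9% in earlier repositioning-chair studies, so the second omission may matter too.

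**Working it through.** **Inputs.** Resolution 25% (control) and 75% (study), and 23 per arm rising to 27 with dropout (section 2.10). Cap of 8 maneuvers, two weeks apart, from week 8, with final follow-up at six months (section 2.6).

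**The plan's own figure.** The protocol gives no figure for the consultation outcome. Its sample size reproduces, with pooled variance, two-sided 5% and 95% power:

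n = [1.960 × √(2 × 0.5 × 0.5) + 1.645 × √(0.25 × 0.75 + 0.75 × 0.25)]² / 0.50² = (1.386 + 1.007)² / 0.25 = 22.9, i.e. 23 per arm (power 95.1%).

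Adding 15%: 23 × 1.15 = 26.45, i.e. 27 per arm. Nothing below changes these figures.

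**Step 1: patients without a value.**

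- At 27 per arm: control 27 × 0.75 = 20.25; study 27 × 0.25 = 6.75. Together this is 27 of 54, half the trial.
- Resolvers at 23 per arm: control 23 × 0.25 = 5.75; study 23 × 0.75 = 17.25.
- The eighth maneuver falls at week 8 + 7 × 2 = 22, before month 6 (about week 26), so patients can reach the cap unresolved within follow-up.

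**Step 2: illustration with no cures on exercises.** Assume a constant success probability p per session, with the section 2.10 rates reached over 8 sessions: p = 1 − (1 − R)^(1/8).

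- Control: p = 1 − 0.75^(1/8) = 0.0353. Study: p = 1 − 0.25^(1/8) = 0.1591.
- Mean sessions among resolvers, 1/p − 8(1 − R)/R: control 28.31 − 24 = 4.31; study 6.29 − 2.67 = 3.62. Difference 0.69.
- Mean sessions in all patients, non-resolvers counted at 8, R/p: control 7.08; study 4.71. Difference 2.36 before rounding.

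**Step 3: allow cures on exercises.** Both arms do eight weeks of exercises before any maneuver, so let a share b resolve on them and need 1 consultation (the negative test at Visit 1). The others have constant success over 8 maneuvers, and resolution after k maneuvers takes k + 1 visits. Non-resolvers are counted at 9. The overall rates stay at 25% and 75%.

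| b | Control − study, resolvers only | Control − study, all patients |
|---|---|---|
| 0 | 0.69 | 2.36 |
| 5% | 0.07 | 2.31 |
| 10% | −0.56 | 2.26 |
| 20% | −1.86 | 2.16 |

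For b = 10%, the resolver means are 3.63 and 4.19, and the all-patient means are 7.66 and 5.39. The all-patient difference hardly moves, while the resolvers-only difference changes sign between b = 5% and b = 10%.

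**Step 4: a pattern in the other direction.** Same rates, but every control resolver resolves at visit 9 and every study resolver at visit 2.

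- Resolvers only: 9 − 2 = 7.0.
- All patients: (0.25 × 9 + 0.75 × 9) − (0.75 × 2 + 0.25 × 9) = 9 − 3.75 = 5.25.

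Here the resolvers-only comparison overstates the saving.

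**The case against.** The strongest reply is that the protocol never says the analysis is limited to resolvers. Section 2.8 commits to the full analysis set and intention to treat, the Abstract describes the secondary outcome as a reduction in healthcare visits without a condition on resolution, and a statistical analysis plan that is not shown could give non-resolvers a value. This stands as far as it goes: a restriction to resolvers is something a reader might infer, not something the text states. It does not remove the defect. The definition appears in three sections, one of them the Visit 3 data item, and it conflicts with the stated analysis set unless a rule is added. A later rule that scores non-resolvers at the cap would count maneuver sessions, not consultations, although section 2.6 itself allows for intermediate visits. If the form holds only the listed item, total use may not be recoverable.

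A reader might also infer that the outcome must understate the saving. Steps 3 and 4 show otherwise: the resolvers-only difference can shrink, reverse or grow, depending on when patients resolve. The shrinkage in Step 2 depends on there being no cures on exercises, whereas section 2.10 expressly includes such cures in the control rate. The 75% is also a design target, not a forecast.

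Finally, this is a secondary outcome with no power claim, and the primary result is unaffected. That limits the seriousness of the point, not its correctness.

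**Conclusion.** The point holds as a badly fixed outcome definition. At the protocol's own rates the variable is undefined for about 75% of controls and 25% of study patients. It can neither be analysed as section 2.8 promises nor answer the healthcare-resource objective. Followed literally, it gives a non-randomized comparison of about 6 with 17 patients, with bias of uncertain direction.

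The count of undefined patients rests only on the 25% and 75% of section 2.10, taken to apply to whichever resolution ends the count. The sizes of the differences rest on assumptions that the protocol does not supply: constant success per maneuver, a chosen share cured by exercises, one consultation per protocol visit, a cap of eight maneuvers in total, and non-resolvers counted at the cap. They show how unstable a resolvers-only comparison would be and are not estimates of the bias.

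The change should be made because a stated secondary objective cannot be answered as defined. The primary outcome and the sample size are not affected.

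**What to change.** In sections 2.5, 2.6 (the Visit 3 item) and 2.8, define the resource outcome as the total number of BPPV-related consultations, scheduled and unscheduled, from randomization to month 6, in every randomized patient whether or not resolved. Report it as a mean difference between arms with a confidence interval.

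Report the number of sessions to resolution as a separate outcome, with non-resolvers censored at the protocol's own 8-repetition cap.

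The cost is small: wording in three sections and a change to the Visit 3 form. The total is not already collected, as a reader might suppose, because Visit 3 lists only consultations needed for resolution. The study period in section 2.2 began in January 2024, so for any patient already past Visit 3 the total would have to be taken from clinic records. Treatment, visit schedule and sample size do not change.
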